#### **11.4.3 Secondary Analyses**

For the secondary analysis, considering the changes of outcome variables from baseline over time either a 2-way repeated measures ANOVA with time as within-subject factor and treatment as between subject factor or a comparable linear mixed effect model (lme) with defined fixed factors (e.g. treatment) and random factors (e.g. patient id) considering potential interactions between factors (e.g. between time and treatment) will be applied to evaluate the potential treatment effect at different time points within the 12-weeks observation period (see 9.2).

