| Study Centre(s):            | Single-centre                                                                                                                                                                                                                                                                                                                                                                                                                                                                                                                                                                                                                                                                                                                                                                |
| Statistical Considerations: | 
Sample size calculation for primary study outcome (<math>\Delta</math>PVS);
 
 
• Normal-distribution check: Shapiro-Wilk test, histograms, QQ-plots;
 
• Homogeneity of variance check: Levene's test;
 
• Primary analysis: Mixed model for repeated measures (MMRM) for primary endpoint analysis;
Association analysis: Pearson's correlation coefficient or Spearman's ranked correlation coefficient;
 
• Secondary analysis: MMRM to evaluate treatment effect at different time points along the observation period or ANCOVA for outcomes, which are only measured at baseline (V2) and at the end of treatment period (V5);
 
• Significance level: <math>p < 0.05</math>;
 
 |
| GCP Statement:              | This study will be conducted in compliance with the protocol, the current version of the Declaration of Helsinki, the ICH-GCP as well as all national legal and regulatory requirements.                                                                                                                                                                                                                                                                                                                                                                                                                                                                                                                                                                              |

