## **8.5 Data collection and follow-up for withdrawn participants**

Patients that withdraw from the study drug will be encouraged to participate in all regular study visits and assessments. Patients that withdraw consent will be included in the intention-to-treat analysis with the measurements that have been obtained until the withdrawal.

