## 11.4 Planned Analyses

### 11.4.1 Datasets to be analysed, analysis populations

Statistical analyses (primary and secondary) will be performed by the investigators with support from a biostatistician using IBM SPSS V25 (Chicago, IL, USA), R statistics software V3.6.1 (R foundation of statistical computing) and GraphPad Prism software package V8.0 (San Diego, CA, USA).

The dataset will comprise all patients initially randomized.

All data will be tested for normal distribution with the Shapiro-Wilk test and by graphical evaluation using histograms and Q-Q-plots.

The homogeneity of variances will be checked with Levene's test.

In case of non-normal distribution, variables will be either logarithmically transformed to approximate

normality before parametric testing will be applied or if applicable a corresponding non-parametric test will be used.

**Note:** The data analysis of the planned prospective observational follow-up study visit (Fig. 1: V6, 12 months after the end of IMP treatment) will not be included in the main study evaluation and analyzed separately to avoid delays to obtain the outcome results of the main study.

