#### **11.4.2 Primary Analysis**

For the primary analysis, a mixed model for repeated measures (MMRM) - will be applied for continuous outcome variables (e.g.  $\Delta$ PVS) to test for a potential treatment effect between groups (DAPA vs. PLA).

**Rationale:** Although the ANCOVA test is considered as statistical 'robust' and 'efficient' test for analysing continuous outcomes requiring covariate adjustment in RCTs [121] and was previously used by others in a comparable study setting [122]. However, the MMRM has the advantage to better handle missing data at random and thus avoids to 'lose' subjects in the data analysis.

For testing of potential associations between outcome variables Pearson's correlation coefficient ( $r$ ) will be used or if case of non-normal distributed data the Spearman's rank correlation coefficient ( $\rho$ ) will be used. A p-value of  $< 0.05$  is considered to indicate statistical significance.

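### Section 11.4.3 and the synopsis plan different analyses for the same secondary outcomes, and 11.4.3 omits the baseline-adjusted one

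*Protocol*

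**What the plan says.** The synopsis (Statistical Considerations) sets out the following for the secondary outcomes: "MMRM to evaluate treatment effect at different time points along the observation period or ANCOVA for outcomes, which are only measured at baseline (V2"; its sentence then names V5 as the second of the two measurements. That is a rule tied to the visit schedule.

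Section 11.4.3 covers the same ground, "considering the changes of outcome variables from baseline over time", but allows "either a 2-way repeated measures ANOVA with time as within-subject factor and treatment as between subject factor" and, as the alternative, "or a comparable linear mixed effect model (lme) with defined fixed factors (e.g. treatment) and random factors (e.g. patient id" as its example of a random factor. ANCOVA does not appear there, and repeated-measures ANOVA does not appear in the synopsis.

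Three other places bear on the choice:

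- Section 11.4.2 prefers MMRM for the primary analysis because "the MMRM has the advantage to better handle missing data at random and thus avoids to 'lose' subjects in the data analysis".
- Section 11.4.1 says: "The dataset will comprise all patients initially randomized".
- Section 8.5 says that patients who withdraw consent are "included in the intention-to-treat analysis with the measurements that have been obtained until the withdrawal".

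On timing, Table 1 marks secondary variables at V2 and V5 only. Section 9.3.2 places PWA/PWV, RVA and FMD at those two visits. Section 9.3.4 adds OpCO and BIA at V3 and V4.

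**The concern.** The protocol gives two plans for one set of outcomes. One has a selection rule. The other is an open choice between two methods that treat incomplete patients differently, so the decision could be taken after the data are seen. The synopsis names macro- and micro-vascular function as the main secondary objectives, and the vascular measurements are the ones for which ANCOVA is present in one text and absent from the other.

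Two things are at stake. For V2/V5-only outcomes it is the precision gained by using the baseline value as a covariate. For outcomes measured at all four visits it is whether patients with a gap in their series stay in the analysis, which is the reason the protocol itself gives for preferring MMRM.

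**Working it through.** **Inputs.** From section 11.2: d = 0.5, two-sided 5% type I error, 80% power, baseline-to-week-12 correlation ρ = 0.6. From the synopsis: 40 per arm. The protocol states no missed-visit rate, so 3%, 5% and 10% per follow-up visit are assumed. Section 11.2 sets d and ρ for the primary outcome; using them for secondary outcomes is an illustration.

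**1. Reproducing the plan's own figure.** A two-sample t-test needs 63.77 per group (stated 63.8), rounded to 64, or 128 in total. Multiplying by 1 − ρ² gives 128 × 0.64 = 81.92 (stated 81.9). The figures agree.

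**2. What 11.4.3 amounts to with two visits.** In a two-way ANOVA with time (V2, V5) within patients and treatment between them, the time-by-treatment term is the difference between arms in mean (V5 − V2). A mixed model with treatment, time, their interaction and a random patient intercept gives the same estimate on complete pairs. If the change itself is the response, there is one change per patient and the comparison is again a t-test on change. So neither option, in the form written, is the ANCOVA of the synopsis.

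**3. Precision for V2/V5-only outcomes.** Relative to the outcome variance σ²:

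- change score: 2(1 − ρ) = 2 × 0.4 = 0.80
- ANCOVA: 1 − ρ² = 0.64
- ratio: 0.80 / 0.64 = 1.25, so 25% more patients for equal precision (128 × 0.80 = 102.4 against 81.9)

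The standardised effects are 0.5/√0.80 = 0.559 and 0.5/√0.64 = 0.625. Power from the t-test at 40 per arm:

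| ρ | Change score | ANCOVA |
|---|---|---|
| 0.4 | 52.2% | 67.4% |
| 0.5 | 59.8% | 72.2% |
| 0.6 | 69.5% | 78.8% |
| 0.7 | 81.4% | 87.1% |
| 0.8 | 93.7% | 95.7% |

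ANCOVA is ahead throughout, and the gap narrows as ρ rises.

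**4. Patients kept for four-visit outcomes if the ANOVA is chosen.** The classical form needs all visits. With a proportion m missed independently at each of V3, V4 and V5, complete cases are 80(1 − m)³:

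| m | Complete V3–V5 | V5 present, 80(1 − m) |
|---|---|---|
| 3% | 73.0 | 77.6 |
| 5% | 68.6 | 76.0 |
| 10% | 58.3 | 72.0 |

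Independence makes the loss large. If the same 10% of patients left before V3 and everyone else completed, 72 would remain rather than 58.

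**The case against.** The strongest reply is that 11.4.3 does not fix the ANOVA. A reader who stops at the first option might infer that secondary outcomes will be analysed by repeated-measures ANOVA and that every patient with a missed visit is dropped. The text does not support that. The second option is a mixed model, which keeps patients with partial data and is close to the synopsis MMRM. For outcomes measured repeatedly the two texts therefore overlap. Loss of patients arises only if the ANOVA is chosen, and only for OpCO volumes and BIA.

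Three further stronger readings also fail:

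- **That the vascular comparisons lose patients or are biased by listwise deletion.** With V2 and V5 only, a missed V3 or V4 costs nothing, and a missing V5 is lost to ANCOVA as well.
- **That baseline is ignored.** Changes from baseline are analysed, so baseline is used, though not as a covariate. The issue is efficiency, not validity.
- **That the analysis misses its target because the interaction test is not the week-12 comparison.** Both texts aim at the treatment effect at several time points, and section 5.2 fixes no week-12 contrast for secondary outcomes.

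It is also fair to say that the magnitudes are borrowed or assumed: no correlation is given for RVA, PWA or FMD, and no missed-visit rate is given at all. The model terms in 11.4.3 are only examples, so a baseline covariate could be added later.

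Finally, model detail for secondary outcomes is often left to the SAP. That would answer a silence. It does not answer two statements in the current protocol that differ, one with a rule and one without.

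**Conclusion.** The point holds as an inconsistency with a practical cost. The synopsis assigns ANCOVA or MMRM by visit schedule. Section 11.4.3 leaves ANOVA or a mixed model open, drops ANCOVA and names no baseline covariate.

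For V2/V5-only vascular outcomes the cost is precision: about 9 percentage points of power at ρ = 0.6 (78.8% − 69.5%) and 2 points at ρ = 0.8, if d = 0.5 and 40 per arm carry over from the primary outcome.

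For OpCO volumes and BIA, the ANOVA option conflicts with the reason for MMRM in 11.4.2 and with the retention of all randomised patients and partial data in 11.4.1 and 8.5. Under the assumed independent 3% to 10% missed per follow-up visit it would keep about 73 to 58 of 80, and more if missed visits cluster in the same patients.

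The primary analysis is not affected.

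**What to change.** Replace the text of 11.4.3 by the synopsis rule:

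- Continuous outcomes measured only at V2 and V5: ANCOVA of the V5 value on treatment and the V2 value.
- OpCO blood volumes and BIA, measured at V2 to V5: baseline-adjusted MMRM with treatment-by-visit contrasts.
- Delete the repeated-measures ANOVA.

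Leave eGFR and NT-proBNP where they are. Section 5.4 lists them as safety outcomes, and 11.4.5 keeps the safety analysis descriptive, without formal inference. Giving them a modelled comparison would create a new contradiction.

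The cost is one paragraph. It needs no new data, visits or budget, because the baseline values are already collected. Section 2.10 counts changes to the form of statistical analysis among those needing ethics committee authorisation, so the change belongs in an amendment and should be settled before unblinding.

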## 6. STUDY DESIGN

### 6.1 General study design and justification of design

#### 6.1.1 General study design

The DAPA-VOLVO study project is a randomized, double-blind, placebo-controlled parallel-group trial to evaluate the superiority of dapagliflozin on top of recommended therapy in comparison to placebo on blood volume profile and vascular function in clinically stabilized heart failure patients after hospitalization/ ambulatory care because of an acute decompensated (congestive) heart failure event. A total of 80 HF-patients (40 patients per each treatment arm) will be recruited at the University Hospital Zurich.

DAPA-VOLVO- Main study:

The main study will comprise of 5 visits at the study site within the study observation period, albeit V1 will be integrated into V2 whenever logistically feasible. The primary goal must be to follow the planned study frame, however if for particular reasons a study patient can only be enrolled in the short-term post hospitalization phase, e.g. due to the patients wish because of stress overload induced by clinical interventions/procedures during the hospitalization/ ambulatory care phase, a note to file should be generated incl. the reason for the 'postponed' study start.

The relative visit schedule should be maintained as planned (see Fig.1, Table 1).

Important: The study information (SI) must be provided to the potential study candidate at least 24 hours prior to V1. The main study ends after the completion of V5, which also represents the end of IMP-treatment.

DAPA-VOLVO- Advanced session(s):

In order to get a better mechanistic insight into the dapagliflozin effect in HF-patients after an ADHF event an optional advanced session(s) program is implemented. The patients can voluntary choose on the informed consent sheet via check box whether they want to participate or not. The program (Fig. 13) comprises additional tests (e.g. CPET) in close proximity to V2 (V2a) and V5 (V5a).

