## **6.2 Methods of minimising bias**

### **6.2.1 Randomisation**

Eligible patients will be randomized to dapagliflozin treatment group or placebo group in a 1:1 allocation ratio using block randomization. Randomization will be performed with a random computerized algorithm using the secuTrial ® software system via interactive response technology (IRT). The investigator or his/her delegate will contact the IRT after confirming that the patient fulfils all the inclusion and none of the exclusion criteria. The IRT will assign a randomization number to the patient, which will be used to link the patient to a treatment arm and will specify a unique medication number for the first package of investigational treatment to be dispensed to the patient. The randomization list is generated by the secuTrial ® software system and responsible staff at the Clinical Trial Center Zurich. The secuTrial ® software system ensures that the randomization list is concealed from the study team and investigators (unless in case of necessary unblinding as depicted in 5.4).

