### 1. ANCOVA:

The calculation is based on a two-step approach for an ANCOVA test setting as proposed by Borm et al. [119].

In a first step, the sample size required for a t-test (type I error probability: 5%, two-sided) was calculated by assuming a moderate effect size ( $d= 0.5$ ) to reach a power of 80%. It revealed a sample size of  $n= 63.8$  per group, which was rounded up to 64.

In a second step, the t-test sample size was multiplied by a 'design factor' ( $z$ ), which was calculated as follows:  $z = (1 - p^2)*n$ ,  $p$  = correlation of the mean of outcome variable  $Y$  at baseline ( $Y_0$ ) and after the treatment period (12 weeks) ( $Y_1$ ), which was set at 0.6,  $n$  = calculated t-test total sample size ( $n= 128$ ).

Subsequently, the ANCOVA-based power analysis revealed a total sample size of 81.9 to reach a power of  $\geq 0.8$ .

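### Section 11.4.3 and the synopsis name different secondary models; run in plain form, those in 11.4.3 could give about 8–13% type I error for week-12 changes in OpCO and BIA outcomes if correlation falls with time

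*Protocol*

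**What the plan says.** Protocol section 11.4.3 covers changes in the outcome variables from baseline and aims to assess the treatment effect at individual time points within the 12 weeks. It leaves two models open. The first is a "2-way repeated measures ANOVA with time as within-subject factor and treatment as between subject factor". The second, given as an alternative with no rule for choosing between them, is "a comparable linear mixed effect model (lme) with defined fixed factors (e.g. treatment) and random factors (e.g. patient id". The section names no sphericity correction and no covariance structure.

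The synopsis (Statistical Considerations) plans the same secondary analysis differently: "MMRM to evaluate treatment effect at different time points along the observation period", with ANCOVA for outcomes measured only at V2 and V5. The abbreviation list has separate entries for lme and MMRM. Section 11.4.2 uses an MMRM for the primary outcome.

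On timing, follow-up visits fall 2, 6 and 12 weeks after treatment start. Table 1 marks secondary variables at V2 and V5 only, but section 9.3.4 adds OpCO and BIA at V3 and V4, so these are measured four times. Section 9.3.2 places the pulse wave, retinal and FMD tests in the V2/V5 session, and 9.3.4 does not list them for V3 or V4.

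**The concern.** A model whose only random term is a patient intercept implies the same correlation between every pair of visits. A repeated-measures ANOVA with one pooled within-patient error uses a single error variance for every change between visits. The visits here are unequally spaced, in patients just stabilised after decompensation, so it is plausible that measurements 12 weeks apart correlate less than measurements 2 weeks apart.

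If so, the baseline-to-week-12 change has the largest true variance and a pooled error understates it, while the baseline-to-week-2 change is overstated. Change from baseline at given time points is what 11.4.3 sets out to test. At stake are the week-12 statements on blood volumes and body water (false positives) and the week-2 statements (lost power). The assumption checks listed in the synopsis and in 11.4.1 (Shapiro-Wilk, plots, Levene's test) would not reveal the problem, because none looks at within-patient covariance.

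**Working it through.** **Inputs.** From section 11.2: "type I error probability: 5%, two-sided", and a correlation between baseline and week 12 "which was set at 0.6". From section 6.1.1: "A total of 80 HF-patients (40 patients per each treatment arm". Visits at 0, 2, 6 and 12 weeks. *Assumed, not in the protocol:* equal variance at all visits, complete data, exponential decay of correlation with time, and a measurement-error share m of 0, 10 or 20% of the variance.

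**The protocol's own figure first.** The t-test calculation gives 63.77 per arm, rounded to 64. Then 128 × (1 − 0.6²) = 81.92, which reproduces the stated 81.9. The protocol states no error rate for 11.4.3.

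**Correlations.** r(t) = (1 − m)·exp(−kt), with k chosen so that r(12) = 0.6. The gaps between visits are 2, 6, 12, 4, 10 and 6 weeks. For m = 0 the correlations are 0.918, 0.775, 0.600, 0.843, 0.653 and 0.775, with mean 0.761. For m = 10% the mean is 0.723, and for m = 20% it is 0.684.

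**Week-12 change.** The true variance of a change is 2σ²(1 − 0.6). A pooled-error or equal-correlation model uses 2σ²(1 − mean r). Therefore:

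- interval width, model over true = √[(1 − mean r)/0.4]
- type I error = 2[1 − Φ(1.96 × that ratio)]

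| Pattern | mean r | Width ratio | Too narrow by | Type I, formula | Type I, simulated |
|---|---|---|---|---|---|
| Decay, m = 0 | 0.761 | √(0.239/0.4) = 0.77 | 23% | 13.0% | 13.0% |
| Decay, m = 10% | 0.723 | √(0.277/0.4) = 0.83 | 17% | 10.3% | 10.2% |
| Decay, m = 20% | 0.684 | √(0.316/0.4) = 0.89 | 11% | 8% | 8.0% |
| Equal correlation 0.6 | 0.600 | 1.00 | 0% | 5% | 5.2% |

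The simulations used null trials with 40 per arm: 4,000 for the m = 20% row and 40,000 for the others.

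**Week-2 change.** The width ratio is √(0.239/0.082) = 1.71 for m = 0 and √(0.316/0.24) = 1.15 for m = 20%, so intervals are about 15–70% too wide.

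**Sensitivity.** At correlation 0.6, autoregressive decay by visit gives 12.8% and decay towards a floor gives 11.1%. A baseline-adjusted equal-correlation model under exponential decay gives 12.2% (11.6% simulated). Across assumed baseline-to-week-12 correlations of 0.3–0.8, the decaying patterns give about 7–14%.

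**What cures it.** When the week-12 contrast has its own error term, or the covariance is unstructured, simulated type I error is 4.9–5.2%. The Greenhouse-Geisser correction brings the overall time-by-treatment test from 6.0–7.2% to 4.7–5.0%, but it does not repair single-visit contrasts built on a pooled error.

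**The case against.** A reader might infer that 11.4.3 imposes equal correlation and so commits the trial to about 13% false positives at week 12. The document does not support that, for four reasons:

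- **The text leaves the model open.** It speaks of random factors in the plural and gives patient id only as an example. An lme can carry further random effects or a residual correlation structure. Covariance detail is commonly left to an SAP, and the MMRM entries name no structure either.
- **The ANOVA needs less than equal correlation.** It requires sphericity, meaning equal variances of the differences between visits. It can also be run with contrast-specific errors, which hold 5%.
- **The decay pattern is assumed.** The 0.6 was set for the PVS sample size, and carrying it over to blood volumes and body water is a further assumption. Nor is 13% a ceiling: about 14% arises at correlations of 0.7–0.8.
- **The reach is narrow.** With only V2 and V5 there is one correlation and nothing to misfit. The week-12 PVS test belongs to the primary MMRM. The between-arm difference in level at week 12, as opposed to change, stays near 5%.

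All of this stands, and it makes the error conditional. It does not dispose of the point. 11.4.3 names concrete models, describes the lme as comparable to the ANOVA, and targets change from baseline, where a pooled error does harm. The synopsis names other models for the same task.

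**Conclusion.** The firm part is the contradiction. For the same secondary analyses, 11.4.3 names repeated-measures ANOVA or lme, while the synopsis names MMRM or ANCOVA.

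The conditional part is the size. It requires both that 11.4.3 be run as a plain random-intercept or pooled-error model and that correlation fall with time between visits. With the protocol's 0.6 and the assumed decay, the week-12 change contrasts for OpCO blood volumes and BIA body water then have intervals about 11–23% too narrow and roughly 8–13% type I error, and the week-2 intervals are about 15–70% too wide. With equal correlations the error is nil. The primary analysis and the retinal, pulse wave and FMD outcomes at V2/V5 are not touched. The point is worth correcting because the current wording permits the weaker analysis and the remedy is cheap. It does not threaten the trial's main conclusion.

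**What to change.** Align 11.4.3 with the synopsis and remove the either/or:

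- For outcomes measured at three or more visits, use an MMRM on the post-baseline visits with unstructured covariance over visits and Kenward-Roger degrees of freedom.
- For outcomes measured only at V2 and V5, use ANCOVA.

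Stating the covariance structure matters, because renaming the model MMRM does not by itself rule out an equal-correlation fit.

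The cost is protocol or SAP wording, with the same data and software. Statistically, an unstructured matrix over three post-baseline visits has six parameters (three variances and three covariances) against two under equal correlation. Eighty patients can support those four extra parameters.
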